**Methods:**

We will include 100 untreated patients with moderate to severe depression (>17 on the Hamilton Depression Rating Scale 17) in a non-randomized open clinical trial. We will collect data from serotonin 4 receptor positron emission tomography (PET) brain scans, functional magnetic resonance imaging (fMRI), electroencephalogram (EEG), cognitive tests, psychometry, and peripheral biomarkers, before (at baseline), during, and after 12 weeks of standard antidepressant treatment. Patients will be treated with escitalopram, and in case of non-response at week 4 or intolerable side effects, offered to switch to a second line treatment with duloxetine. Our primary outcome (treatment response) is assessed using the Hamilton depression rating subscale 6-item scores at week 8, compared to baseline. In a subset of the patients (n = ~40), we will re-assess the neurobiological response (using PET, fMRI, and EEG) 8 weeks after initiated pharmacological antidepressant treatment, to map neurobiological signatures of treatment responses. Data from matched controls will either be collected or is already available from other cohorts.

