**Discussion:**

The extensive investigational program with follow-up in this large cohort of participants provides a unique possibility to (a) uncover potential biomarkers for antidepressant treatment response, (b) apply the findings for future stratification of MDD, (c) advance the understanding of pathophysiological underpinnings of MDD, and (d) uncover how putative biomarkers change in response to 8 weeks of pharmacological antidepressant treatment. Our data can pave the way for a precision medicine approach for optimized treatment of MDD and also provides a resource for future research and data sharing.

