## Introduction

Major Depressive Disorder (MDD) is one of the most severe and common brain disorders worldwide with a huge impact on life quality and socioeconomic status (1, 2). It has been linked to serotonergic dysfunction, cognitive disturbances, brain network dysfunction, vulnerability to stress, neuro-inflammation, and gene by environment factors. Still, the understanding of the pathogenesis remains limited. Guidelines for MDD treatment selection are still predominantly based on simple clinical observations about overall MDD severity, and in the case of recurrent depressive episodes, it is also based on personal patient history of treatment responses. Conventional medical treatment is mainly based on intervention of the monoaminergic system in the brain, in particular the serotonin (5-HT) system. Selective serotonin reuptake inhibitors (SSRIs) act through blockage and subsequent downregulation of the serotonin transporter (SERT) (3), which presumably induces increased extracellular 5-HT levels. However, robust evidence for a central 5-HT hypofunction in patients with MDD *in vivo* is lacking (4). Roughly one third of patients suffering from MDD do not respond sufficiently to 5-HT acting drugs (5, 6), suggesting a diverse pathophysiology. The diagnostic criteria for MDD may cover a heterogenous collection of various biological entities and consequently, it is not surprising that a “one size fits all” treatment strategy is suboptimal (7). Currently, the time from starting to administer a potentially efficacious drug until it can be determined if the clinical response is satisfactory is, at best, 4–6 weeks. In clinical practice, the lack of convenient and accurate tools (e.g., quantitative and/or biological) to predict treatment response prolongs the delay from diagnosis to effective treatment and constitutes a major challenge for both clinicians and patients. Therefore, stratification of subtypes and a shift toward precision medicine, e.g., through identification of predictors of treatment response, so-called biomarker(s) that can help optimize treatment choice, is of paramount importance. Candidate biomarkers could be related to neurotransmission, specific neural networks or structural alterations in specific brain regions that can be detected by brain imaging modalities such as positron emission tomography (PET), functional magnetic resonance imaging (fMRI), and electroencephalogram (EEG) or altered biophysiological or cognitive functions (4, 8). It has also been suggested that rather than a single biomarker, an algorithm involving a set of biomarkers may prove useful to subgroup patients and predict their response to certain treatment strategies in MDD (9). Several biomarkers derived from prior large studies such as iSPOT-D, EMBARC, and CANBIND for prediction of drug response in MDD have been proposed (10–12). Here, we use multimodalities (PET, fMRI, and EEG, cognitive testing, psychometrics, and peripheral biomarkers) as part of a deep phenotyping and as a unique feature to our trial, we study modes of action in the brain on a neurotransmitter level. Thus, our trial contributes with novel insights as well as provide a dataset for cross-validation of other identified predictors of psychopharmacological antidepressant treatment response. In a non-randomized, longitudinal, open clinical trial, patients with moderate to severe depression will be treated with SSRI following Danish guidelines. In order to map neurobiological signatures of treatment, we will re-examine a subset of the cohort with neuroimaging and EEG after 8 weeks of SSRI treatment and assess cognitive changes after 12 weeks. This clinical trial is part of a larger research initiative, “NeuroPharm”, which addresses pertinent and basic questions regarding human brain disease mechanisms and seeks to predict brain responses to categories of neuro-modulatory interventions as well as treatment efficacy (www.np.nru.dk). We anticipate that this study will critically advance and inform future stratification strategies, further uncover pathophysiological and treatment mechanisms and, hopefully, guide future precision medicine approaches to optimize treatment strategies for patients suffering from MDD.

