Sexual dysfunction (e.g., low sexual desire, arousal difficulties, and anorgasmia) is a prominent feature of MDD, which often leads to a decline in quality of life (61, 62). Lack of interest to what is usually pleasurable, i.e., anhedonia, is a core symptom in MDD and may also be reflected in reduced sexual desire/interest. Sexual dysfunction, in particular anorgasmia and sexual arousal difficulties may further be linked to serotonergic dysfunctions (63) as seen in MDD. As a complicating factor, impaired sexual health related to MDD may worsen with antidepressant treatments targeting the 5-HT system. For example, in a group of 704 patients with MDD treated with an antidepressant drug (SSRI) or serotonin-norepinephrine reuptake inhibitor, about half of them developed or experienced worsening in their decreased sexual desire as a side-effect, which was also associated with reduced quality of life, lower self-esteem and adverse effects on mood and partner relations (62). We currently do not know which patient characteristics predict sexual dysfunction in response to SSRI treatment. However, differences in individual serotonergic brain architecture and/or serotonergic response to antidepressant treatment (e.g., SSRI) may play a role. In this study, we aim to map the frequency and predictors of SSRI induced sexual dysfunction and determine if serotonergic tonus (measured by 5-HT_4_R PET binding) pre-treatment, or changes in response to SRRI treatment, is associated with sexual desire and/or development of SSRI-induced sexual dysfunction in MDD.

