Previous findings from our group have repeatedly demonstrated a coupling between key features of the 5-HT system and hypothalamus- pituitary- adrenal axis (HPA-axis), which regulates the release of the stress-hormone cortisol (64). Such HPA-axis dynamics can be measured by the cortisol awakening response. Our results support that both serotonin transporter availability (65), and serotonergic tone or direct capacity for 5-HT_4_R agonism (64) support a healthy cortisol response to HPA-axis stimuli. A well-functioning and dynamic HPA-axis is critical for coping with everyday life stressors, and HPA-axis dysregulation is a prominent feature of MDD. Although heightened CAR is associated with relapse of depressive episodes in patients with a history of depression (66), in the more advanced depressed stages, i.e., chronic depression, HPA-axis dynamics are blunted as opposed to recent-onset depression (67). Notably, normalization of the HPA-axis in response to SSRI treatment appears to protect against relapse (68). Thus, the SSRI treatment response is likely to depend on restoring HPA-axis dynamics at least in a subgroup of MDD patients. In this trial, we will assess CAR in patients with MDD, the effect of SSRIs on CAR, investigate its association with baseline 5-HT_4_R distribution, as well as evaluate CAR as a predictor of antidepressant treatment outcome.

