### Participants

Patients are recruited from a central referral center within the mental health services in the Capital region of Denmark or directly referred from one of five general practitioners in collaborations with the study group (see **Figure 2** (CONSORT) for details). Data from healthy controls for the purpose of baseline comparisons to patients with MDD are available from a pre-existing database on site (71). The healthy control reference population will be supplemented with newly recruited healthy controls from a local volunteer database (www.nru.dk), as necessary.

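### Two secondary aims, on the cortisol awakening response and on sexual dysfunction, are worded as SSRI effects that a one-group open design cannot identify

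*Protocol article*

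**What the plan says.** The Abstract (Methods) describes 100 patients enrolled "in a non-randomized open clinical trial". Under Clinical Procedure After Treatment Initiation, every patient starts escitalopram. At week 4, early non-responders or patients with unacceptable side effects are offered duloxetine, which the article classes as a serotonin-norepinephrine reuptake inhibitor.

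The Participants section introduces the control group as "Data from healthy controls for the purpose of baseline comparisons to patients with MDD", and Baseline Assessments Before Treatment gives controls the baseline programme only. No repeat assessment of controls is described.

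The Introduction sets two aims in terms of what the drug does:

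- Cortisol: "we will assess CAR in patients with MDD, the effect of SSRIs on CAR". The Saliva section and Table 2 schedule sampling at baseline and week 8.
- Sexual function: "we aim to map the frequency and predictors of SSRI induced sexual dysfunction". Table 1 schedules the Changes in Sexual Functioning Questionnaire (CSFQ) at baseline and weeks 4, 8 and 12.

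For each outcome the same section names a competing source of change. It states "Sexual dysfunction (e.g., low sexual desire, arousal difficulties, and anorgasmia) is a prominent feature of MDD", and it describes dysregulation of the HPA axis as a leading feature of depression that differs between recent-onset and chronic illness.

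**The concern.** An effect of an SSRI is a contrast between what happens on the drug and what would have happened without it. The trial observes only the first. A shift in CAR from baseline to week 8 may be the drug, the remitting episode, or both. Sexual dysfunction seen on treatment may be caused by the drug, may persist or worsen with the illness, or may be hidden because recovery improves function while the drug impairs it. The error can therefore go in either direction.

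The duloxetine option adds a second difficulty. Even if natural recovery were set aside, change at weeks 8 and 12 would not be purely an SSRI effect. Those who switch are selected by poor response or by side effects, so the mixture of drugs is not random.

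What is at stake is the conclusion. As worded, an uncontrolled before-after change could be reported as an effect of SSRIs, and a frequency as a rate of harm caused by SSRIs.

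**Working it through.** The plan gives no figure for either aim. Its sample size concerns 5-HT4 receptor binding and plays no part here. The check is whether the planned data can determine the quantity each aim names.

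**Step 1. Needed against available.**

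| Aim | Needed to attribute change to an SSRI | Scheduled in the article |
|---|---|---|
| Effect of SSRIs on CAR | CAR over 8 weeks in comparable patients without the drug | CAR in treated patients, baseline and week 8 |
| SSRI-induced sexual dysfunction | CSFQ course in comparable patients without the drug | CSFQ in treated patients, baseline and weeks 4, 8, 12 |
| Either, for SSRIs specifically | Exposure to an SSRI only | Escitalopram, with duloxetine possible from week 4 |

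Healthy controls cannot fill the gap. They are seen once, and they have no depressive episode to recover from.

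**Step 2. Why treated patients alone do not settle it.** Let x be a baseline marker and e random variation, both standard normal. Write the change in a treated patient as

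change = (aN + bN·x) + (aD + bD·x) + e,

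where N is natural course and D is drug. One treated group reveals only the sums aN + aD and bN + bD. The drug effect is aD. The extent to which the marker identifies who benefits from the drug is bD. Neither can be recovered from the sums.

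**Step 3. Numerical illustration.** The values are assumed, not taken from the article. All three cases have aN + aD = 1 and bN + bD = 0.5. They were simulated with 400,000 patients. The AUC is for x discriminating a change above 1, and units are the SD of e.

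| Case | aN, bN | aD, bD | Mean change, treated | AUC of marker, treated | True drug effect | Drug benefit at x = +1 minus x = −1 (2·bD) |
|---|---|---|---|---|---|---|
| Recovery only | 1, 0.5 | 0, 0 | 1.00 | 0.704 | 0 | 0 |
| Drug only | 0, 0 | 1, 0.5 | 1.00 | 0.704 | 1.0 | 1.0 |
| Half each | 0.5, 0.25 | 0.5, 0.25 | 1.00 | 0.704 | 0.5 | 0.5 |

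The observable results are identical, while the drug effect runs from none of the change to all of it. This is a failure of identification and does not shrink as the sample grows. The last column also shows that a marker can predict outcome in treated patients equally well whether it is purely prognostic or marks benefit from the drug.

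**Step 4. What week 4 offers.** The treatment section places the switch offer at the week-4 visit, where CSFQ is also collected. That measurement, if completed before any switch, is the only follow-up CSFQ that avoids mixing the two drugs. It still does not separate escitalopram from natural recovery. CAR has no week-4 sample.

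**The case against.** The strongest reply is that prediction of outcome among treated patients is a valid one-group aim and is the trial's main purpose. The article's Discussion says outright that specific treatment efficacy is not being investigated. Hypothesis 2 is already worded in time rather than cause, and hypothesis 3 compares remitters with non-responders. The Statistical Analyses section plans to relate change in biomarkers to clinical outcome, so change analyses need not rest on a bare before-after mean. All of this stands, and it protects the primary analysis. It does not reach the two phrases at issue, which ask about effect and are not qualified by the efficacy disclaimer.

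A reader might infer four stronger points that the article does not support:

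- *That the trial sets out to show which drug to choose.* The sentence containing "biomarker(s) that can help optimize treatment choice, is of paramount importance" is background on what the field needs. Where the trial's own contribution is described, guidance of treatment is hedged and placed in the future.
- *That a known share of remitters would have remitted anyway.* The article gives no untreated remission rate, so no such share can be calculated.
- *That all sexual dysfunction present at baseline would be counted as induced.* No passage says so. Baseline CSFQ is scheduled, and the Introduction speaks of development of dysfunction, which suggests a baseline reference.
- *That adjusting for change in HAMD_6 would isolate the drug effect.* That change occurs after treatment starts and may lie on the drug's own path, so it cannot replace a comparator.

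**Conclusion.** The point holds for two secondary aims: the effect of SSRIs on CAR, and the frequency and predictors of SSRI-induced sexual dysfunction. As worded, neither can be answered by this design. The size of the possible error cannot be estimated from the article; logically, the drug's share of the observed change is unrestricted.

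The conclusion rests on the single open treated group, the baseline-only role of controls, the article's own statements that depression disturbs both outcomes, and the duloxetine option. It needs no assumption about recovery rates; the simulation only illustrates the argument. Appendix 1, which lists hypotheses for the other modalities, is not in the text at hand and may word them differently.

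The primary outcome, the sample size and the remitter versus non-responder analysis are unaffected. Baseline predictors remain legitimate predictors of outcome under treatment, with the limit that they may be purely prognostic.

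**What to change.** 1. Restate the cortisol aim as change in CAR during antidepressant treatment.
2. Restate the sexual function aim as frequency and predictors of treatment-emergent sexual dysfunction, defined as new onset or worsening from baseline CSFQ.
3. If a statement specific to escitalopram is wanted, report the week-4 CSFQ separately from weeks 8 and 12, and confirm that it was completed before any switch. Describe it as change on escitalopram, not as its effect.
4. State in the Discussion that neither a drug effect nor drug selection can be concluded without a comparator group, and that baseline predictors are predictors of outcome under treatment which may be purely prognostic.

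All the data are already scheduled, and no visit, sample or patient is added. The cost is wording, one endpoint definition and a more modest claim.

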## Materials and Methods

**Figure 1** shows a flowchart of the scheduled data collection over the 12 weeks of pharmacological drug treatment of patients with MDD. Healthy controls (HC) will be recruited as specified below. Patients will be examined before (at baseline; week 0) and after 1, 2, 4, 8 and 12 weeks of SSRI treatment has been initiated. Depression-severity will be monitored by the Hamilton Depression Rating scale 17 items (HAMD_17_) and its subscale of 6 items (HAMD_6_) (69). A subset of patients will be offered re-examination with PET, fMRI, and EEG after 8 weeks of treatment, to assess changes from baseline and its association to treatment response. Patients from the whole spectrum of treatment responses (from poor to excellent) will be invited in a continuous fashion for this part of the study until allotted re-examinations are completed. All patients will also repeat cognitive testing at week 12. The power analysis in preparation of the study was primarily anchored to the PET modality. We estimated that we needed to include 100 patients to reach a statistical power of 80% to detect an association between treatment response (binary classification, i.e., remitters vs non-responders, see response-definition below) and baseline 5-HT_4_R non-displaceable binding potential (BP_ND_). These calculations were based on an expected 20% maximum drop-out, ~50% remission rate after 8 weeks of treatment (5, 6) and an expected difference of 8% in 5-HT_4_R binding between remitters and non-responders, corresponding to the previously found effect sizes on 5-HT_4_R change in BP_ND_ after fluoxetine treatment (18). Calculations were further based on an average BP_ND_ of 0.71 and a standard deviation of 0.073 (18, 70). With a rescan subgroup of approximately 40 patients, and a Gaussian distribution of change in BP_ND_ with an SD of 0.08 (log scale), we had an expected power of 80% to identify a significant association between longitudinal changes in BP_ND_ and changes in HAMD_6_ (i.e., secondary clinical outcome, continuous scale).

**Figure 1 f1:**
[figure not shown]
Flowchart of study trial assessments for patients with MDD.

### Participants

Patients are recruited from a central referral center within the mental health services in the Capital region of Denmark or directly referred from one of five general practitioners in collaborations with the study group (see **Figure 2** (CONSORT) for details). Data from healthy controls for the purpose of baseline comparisons to patients with MDD are available from a pre-existing database on site (71). The healthy control reference population will be supplemented with newly recruited healthy controls from a local volunteer database (www.nru.dk), as necessary.

**Figure 2 f2:**
[figure not shown]
Flow diagram (CONSORT) of the NeuroPharm trial.

#### Inclusion Criteria for Patients

Patients between 18 and 65 years of age with a moderate to severe, single, or recurrent episode of MDD consistent with the Diagnostic and Statistical Manual of Mental Disorders -5 (DSM-5) and International Statistical Classification of Diseases and Related Health Problems -10 (ICD-10) criteria will be recruited by a trained clinician. Inclusion requires a total score of >17 on HAMD_17_ at baseline and the diagnose is confirmed by using the diagnostic tool Mini International Neuropsychiatric Interview (72). In addition, all patients are diagnostically verified by a specialist in psychiatry before final inclusion.

#### Exclusion Criteria for Patients

Patients with a duration of their present depressive episode exceeding two years are not included. No more than one antidepressant treatment attempt in the current episode prior to inclusion is allowed and only patients with no antidepressant medication within the last two months are eligible. Patients with known contraindications or previous non-response to an SSRI drug after an adequate trial as well as a prior or present history of other primary axis I psychiatric disorders are not included, i.e., MDD must be the primary diagnosis. Other exclusion criteria are: severe somatic illness; substance or alcohol use disorder; insufficient language skills to undergo clinical assessments; acute suicidal ideation or psychosis; patients who are deemed by a psychiatrist to require other forms of antidepressant treatments; pregnancy or breast feeding; use of any CNS drug that cannot be washed out prior to participation (e.g., metoclopramide, ondansetron, serotonergic migraine medicine, clonidine); medical conditions interfering with measurements, contraindications for PET and/or MRI scans; exposure to radioactivity >10 mSv within the last year; severe sensory or intellectual impediments interfering with comprehension of procedures or assessments and lastly any history of brain injury (i.e., loss of consciousness and amnesia or symptoms of concussion disorder).

#### Inclusion and Exclusion Criteria for Healthy Controls

Enrolled HC will be sought to match the patient population by gender and age distribution. All HC will be screened for MDD using a self-reporting questionnaire (major depression inventory) (73). The HC meet the same inclusion and exclusion criteria as required for patients apart from psychiatry related issues (e.g., no current or history of mental illness or unstable somatic condition).

### Treatment and Investigation Program

#### Baseline Assessments Before Treatment

Each patient will receive a basic physical screening including somatic status, routine blood samples, electrocardiogram including QTc interval and collection of toxicology urine tests [The Rapid ResponseTM Multi-Drug Test Panel (Urine)] for detection of drug abuse within the last month. Women are screened for pregnancy through self-reported use of contraceptives and a pregnancy urinary test if relevant. All study-participants will undergo baseline assessments of brain imaging with 11C-SB207145 PET and fMRI; EEG-examination; cognitive testing, collection of questionnaires and biological material (venous blood, urine, and saliva) as specified below. All HC will receive corresponding baseline assessments.

